#### Forecast Execution Dates

Inititation of patient recruitment: June 2023;End of patient follow-up period: December 2024;Publication of results: June 2025.

### 2.4. Treatments

#### 2.4.1. Intervention Group (TAU + ACT)

ACT is a new form of cognitive behavioral therapy (CBT) with a specific focus on mindfulness and acceptance of difficult emotional experiences. It is an evidence-based behavioral therapy that has been found to be effective in treating chronic pain [57]. This therapy emphasizes the need to accept aversive thoughts and feelings, rather than trying to control them. It also promotes a commitment to acting towards personal values, which can lead to a more meaningful and fulfilling life. This is achieved by developing “psychological flexibility” through key processes, such as acceptance, differentiation of self from aversive thoughts and emotions, cognitive defusion (i.e., the ability to observe one’s own thoughts and sensations as temporary events, without necessarily considering them to be true or reflecting oneself), identifying and taking actions based on personal values, being in the present moment, developing an “observing self”, and taking committed action that aligns with personal values. There is evidence that trying to control or change pain can be counterproductive and can lead to increased distress and decreased functionality and quality of life [58,59]. ACT can be an effective treatment for promoting psychological acceptance and flexibility in relation to chronic pain, which can be challenging to modify [60]. The ACT program will be conducted at the Hospital del Mar Pain Unit online (preferably) or in person and will consist of 8 sessions, held once a week, each lasting 90 min. The therapy will last 8 weeks, and each group will have a maximum of 15 participants. The principal investigator ([name]), a psychiatrist with specialization in ACT, will oversee delivering the treatment sessions. ACT will be based on the Vowles et al. protocol [61]. To monitor treatment within ACT, the sessions will be video-taped. An expert in ACT will rate adherence to treatment by revising the videotapes of therapy sessions. A random sample of tapes will be rated using the Acceptance and Commitment Therapy Fidelity Measure. The ACT-FM is a 25-item measure that captures 4 areas: therapist stance, open response style, aware response style, and engaged response style (each split into ACT consistent and ACT inconsistent items, making 8 sections in all). Items are rated on a 4-point scale from 0 (“behavior never occurred”) to 3 (“therapist consistently enacts this behavior”) [62].

Table 1 below shows the contents of the 8 sessions (Session 1: Presentation of the general ACT concept; Session 2: Value analysis I; Session 3: Value analysis II; Session 4: Value analysis III; Session 5: Values and feelings; Session 6: Drink one direction; Session 7: Dare and change; Session 8: Ready to act with ACT).

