### 2.2. Participants and Sample Size

The sample size was estimated through R with R Studio using the package “pwr.t.test” version 4.3.0. This sample size was determined to achieve a power of 80%, a significance level of 5%, and a treatment effect size based on Cohen’s *d* of 0.64 and 0.73 for pain interference (BDI) at post-treatment and at follow-up, respectively [48]. Considering a dropout rate of 30% [48,49,50,51], it will be necessary to include 51 subjects in each study arm. A total of 102 patients with degenerative lumbar pathology who are candidates for lumbar surgery from the Spine Unit of Hospital del Mar (Barcelona, Spain) will be recruited for this study.

Patients who have been scheduled for surgery in the Spine Unit and who have been diagnosed with degenerative pathology that also present psychosocial risk factors for CPSP, as determined by screening questionnaires, will be assessed by the Pain Unit psychiatrist starting June 2023 and will be recruited if they meet the selection criteria. Inclusion criteria will be (a) age 18–80 years, (b) adequate understanding of Spanish or Catalan, (c) meeting the diagnostic criteria for the LBP/degenerative low back pathology that indicates a candidate for first surgical treatment according to the clinical history (International Classification of Diseases [ICD]-10 codes for surgical and diagnostic processes) [52], (d) presence of psychosocial risk factors for CPSP, (e) having an internet connection on a smartphone, tablet, or computer to be able to participate in online therapy, and (f) giving authorization by signing informed consent. Specifically, the psychosocial risk factors associated with CPSP are anxiety, depression, catastrophizing, and fear of movement [35,36]. During the outpatient visit to the Spine Unit, and once the surgical intervention has been proposed and accepted by the patient, the patient will complete three self-administered questionnaires: The Hospital Anxiety and Depression Scale (HADS), Pain Catastrophism Scale (PCS), and Tampa Scale of Kinesiophobia (TSK-11). To select the participants, the cut-off points are high in relation to the HADS (cut-off point ≥ 11), PCS (cut-off point ≥ 24), and TSK-11 (cut-off point ≥ 27), which are based on what was suggested by the authors and reviewers of the adaptations of each questionnaire [53,54,55].

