### 2.6. Statistical Analysis

Data analyses will be carried out using the statistical packages SPSS v26.0, R with R Studio v4.0.2, and MPlus v7.4. Comparative analyses of continuous data will be performed using the Student’s *t* test or their non-parametric equivalents (i.e., Mann–Whitney U or Kruskal–Wallis test), depending on the characteristics inherent to the variables under study. The Chi-Square test or Fisher’s exact test will be used, as appropriate, for categorical variables. The Bonferroni correction will be applied in all post hoc tests. In all statistical tests performed with the outcome variables, a statistical significance level of 0.05 will be used. In adherence with CONSORT recommendations, potential baseline differences in sociodemographic and clinical characteristics are considered irrelevant after randomization and, as a result, were not included as covariates in the analyses of RCT outcomes.

The main analysis will compare the effect ACT compared to TAU on the primary outcome (pain intensity and pain interference at 12-month follow-ups). All data analyses will be carried out following an intention-to-treat (ITT) principle, that is, regardless of protocol adherence. Then, we will compute analysis of the primary outcome post-treatment and analysis of the secondary and treatment process outcomes at post-treatment and at 12-month follow-up. The analyses will be replicated from a per-protocol approach. Multi-level, linear mixed models will be created using the restricted maximum likelihood method for the estimation of parameters. The effect sizes will be calculated according to Cohen’s *d*. A 5% significance level will be used in all 2-tailed tests, applying the Benjamini–Hochberg correction for multiple comparisons (to reduce the risk of false positives).

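### The sample size makes no allowance for clustering within the ACT therapy groups, and the multi-level model does not name therapy group as a level

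*Protocol article*

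**What the plan says.** Section 2.4.1 sets out ACT as eight weekly 90-minute sessions: "The therapy will last 8 weeks, and each group will have a maximum of 15 participants". The Discussion confirms the group format. One psychiatrist leads all sessions. Section 2.4.2 describes TAU as medication and routine follow-up for the individual patient, with no groups.

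Section 2.2 gives the method for the sample size: "The sample size was estimated through R with R Studio using the package “pwr.t.test” version 4.3.0". The inputs are 80% power, a 5% level and Cohen's d "of 0.64 and 0.73 for pain interference (BDI) at post-treatment and at follow-up, respectively". With 30% dropout the result is 51 per arm. No ICC, therapy group or design effect is mentioned.

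Section 2.6 describes the analysis: "Multi-level, linear mixed models will be created using the restricted maximum likelihood method for the estimation of parameters". It does not say what the levels are. It also states: "A 5% significance level will be used in all 2-tailed tests".

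**The concern.** Patients who attend the same therapy group share sessions, discussion and group dynamics, so their later outcomes may be correlated. Individual randomisation does not remove this, because the correlation arises after allocation. It occurs in one arm only, so the design is partially nested.

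Two things are at stake. First, the stated power rests on independent patients and is too high for any positive ICC. Second, if the primary model has no therapy-group term, the standard error of the ACT–TAU contrast is too small, the confidence interval is too narrow and the type I error exceeds 5%. The term multi-level does not settle this: each patient has five visits, and visits within patients already make a model multi-level.

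**Working it through.** **Inputs from the protocol.** 51 per arm, d = 0.64 and 0.73, 80% power, 5% level, 30% dropout (section 2.2); two-sided tests (section 2.6); at most 15 per ACT group (section 2.4.1).

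**Assumptions.** ICC of 0.01, 0.05 or 0.10 (none is given); equal total SD of 1 in both arms; equal group sizes.

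**Step 1: reproduce 51.** A two-sided two-sample t-test at d = 0.64 with 80% power needs 39.3 per arm. 39.3 × 1.3 = 51.1, which matches 51. The whole figure is thus accounted for by independent patients plus dropout inflation, and nothing is left for a design effect.

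**Step 2: groups.** 51/15 = 3.4, so at least 4 groups. Analysed per arm: 51 × 0.70 = 35.7, or 36. With 4 groups that is m = 9 per group.

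**Step 3: formulas.** The design effect applies to the ACT arm only:
- DE = 1 + (m − 1) × ICC
- SE = √(1/36 + DE/36)
- ratio of true to independent-patient variance: R = (1 + DE)/2
- power from the noncentral t with noncentrality d/SE and 70 df (the large-df case)
- true size of a test that ignores groups: 2 × [1 − Φ(1.96/√R)]

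**Step 4: results for 4 groups of 9.**

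| ICC | DE | R | SE ratio √R | Power, d = 0.64 | Power, d = 0.73 | True size if groups ignored |
|---|---|---|---|---|---|---|
| 0 | 1.00 | 1.00 | 1.00 | 76% | 86% | 5.0% |
| 0.01 | 1.08 | 1.04 | 1.02 | 75% | 85% | 5.5% |
| 0.05 | 1.40 | 1.20 | 1.10 | 69% | 80% | 7.4% |
| 0.10 | 1.80 | 1.40 | 1.18 | 62% | 73% | 9.8% |

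The drop from 80% to 76% at d = 0.64 with ICC 0 is not clustering. It arises because multiplying by 1.3 does not offset a 30% loss (39.3/0.70 = 56.2), and it is a separate issue.

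**Step 5: smaller groups.** Fifteen is a ceiling. With 9 groups of 4 analysed, DE = 1.03, 1.15 and 1.30, and R = 1.015, 1.075 and 1.15. True size is then 5.2%, 5.9% and 6.8%.

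**Step 6: the cost of few groups.** With 4 groups the Satterthwaite df are (v₁ + v₀)²/[v₁²/3 + v₀²/35], where v₁ = DE/36 and v₀ = 1/36. This gives about 10, 8 and 7 df at ICC 0.01, 0.05 and 0.10. Power becomes 67%, 59% and 51% at d = 0.64, and 78%, 71% and 62% at d = 0.73.

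**The case against.** A reader might infer that the planned models treat all patients as independent, so that the intervals are bound to be too narrow. The document does not support that. Section 2.6 calls the models multi-level and neither names nor excludes a therapy-group level. The article is condensed, and random-effects structure is commonly left to an analysis plan, which is not shown here. Narrow intervals and an inflated type I error therefore need two conditions: therapy group is left out, and the ICC is above 0. A reader might also infer fixed group membership from the sequential session programme, but the protocol does not say whether membership is fixed or rolling. The point needs only that patients share groups.

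The size of the effect is also open to challenge. The ICC is assumed. Four groups is the fewest possible and so the unfavourable end. One therapist delivers all sessions, so differences between therapists add no clustering. At ICC 0.01 the loss is only one to two points of power. At d = 0.73, the follow-up effect size, power is still about 80% at ICC 0.05 with large df.

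All of that stands as a limit on the size. It does not touch the sample-size statement, which the protocol itself makes and which contains no allowance for the groups.

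**Conclusion.** The point holds in two parts of different strength. Without condition on the analysis model, the sample size ignores the therapy groups, so planned power is overstated for any positive ICC. On the plan's own t-test basis, with 36 analysed per arm and 4 groups, the loss from clustering ranges from one or two points at ICC 0.01 to about 13 to 15 points at ICC 0.10. Conditionally, if the primary model omits therapy group, the true size of a nominal 5% test lies between about 5.2% (small groups, ICC 0.01) and 9.8% (groups of 9, ICC 0.10).

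The figures rest on an assumed ICC, equal group sizes and 30% loss in each arm. The change should be made, but the point does not invalidate the trial: its effect runs from negligible to material, depending on a quantity the protocol does not give.

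**What to change.** 1. Record the therapy-group identifier for every ACT patient. Without it the correlation cannot be modelled later.
2. State in section 2.6 that the primary mixed model has a random therapy-group effect in the ACT arm only, with each TAU patient a cluster of one, and Satterthwaite or Kenward–Roger degrees of freedom.
3. Report the estimated ICC with the primary result.
4. Restate the power in section 2.2 across ICC 0.01 to 0.10 for both d = 0.64 and d = 0.73, giving the expected number and size of groups.

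The cost is one data field, one variance term and some wording. The statistical price is wider intervals and lower stated power, and it is not trivial: only about 4 groups would inform the group variance and the degrees of freedom. Step 6 of the working shows how much this takes off, and the group variance itself will be imprecisely estimated.

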#### 2.4.2. Control Group (TAU)

The control group (TAU) in this study primarily consists of medication prescription and routine follow-up according to the symptoms of each patient. Patients in the control group may also receive ACT treatment if deemed appropriate and recommended by healthcare providers after the study is finished, if they so choose.

### 2.5. Study Measures

Participants in the intervention group (TAU + ACT) and the control group (TAU) will complete the instruments described below. The Table 2 shows the time points at which study measures will be administered.

#### 2.5.1. Measures

This will be used to gather general and clinical information about the patient, including age, educational level, marital status, and years since the diagnosis of LBP, among others.

##### Clinical Features and Screening Measures

The baseline visit of the study will include a clinical examination by a psychiatrist ([name]) from the Pain Unit of Hospital del Mar (Barcelona, Spain) to diagnose mental disorders, using ICD-10 diagnostic criteria and following the usual protocol of the Pain Unit psychiatrists. The examination of the patients by the orthopedic specialist and neurosurgeons of the Spine Unit of the Hospital del Mar will be used to diagnose disorders at the level of the lumbar spine and the type of surgical intervention, using ICD-10 diagnostic criteria, which will be recorded in our protocol.

##### Primary Outcome Measure

The Brief Pain Inventory (BPI) [63,64] is a self-report measure that assesses chronic pain in a multidimensional way. It provides information on pain interference (primary outcome) and pain intensity (secondary outcome) with patients’ daily functioning and activities. An abbreviated version of 11 items is available. The first 4 items evaluate the pain intensity in the last 24 h, ranging from 0 (no pain) to 10 (the worst pain imaginable). Subsequently, 7 items (i.e., general activity, mood, ability to walk, ability to work including domestic work, relationships with other people, sleep, and ability to enjoy the life) are assessed from 0 (does not disturb) to 10 (totally disturbs) to report the degree of involvement of chronic pain in these areas of the person’s functioning. The higher the score in the areas of the questionnaire, the greater the intensity of perceived pain, as well as the greater degree of involvement of chronic pain in the functioning of the person in the various areas explored.

##### Secondary Outcome Measures

The Hospital Anxiety and Depression Scale (HADS) [65,66] is a 14-item questionnaire, consisting of two 7-item sub-scales, one for anxiety (HADS-Anx, odd items) and another for depression (HADS-Dep, even items). Symptoms are evaluated on a 4-point Likert scale (range 0–3) with different response options. The time frame is within the previous week. The score for each sub-scale is obtained by adding the values of the respective items. The same cut-off points are proposed for the two sub-scales (0–7 normal; 8–10 possible involvement; ≥ 11 clinical problem).

The Pain Catastrophizing Scale (PCS) [67] is a scale with 13 items that includes 3 dimensions: rumination (items 8, 9, 10, and 11), magnification (items 6, 7, and 13) and helplessness (items 1, 2, 3, 4, 5, and 12). Each item is scored from 0 (not at all) to 4 (always) and the total scores range from 0 to 52, with higher scores indicating greater pain catastrophizing.

The Tampa Scale of Kinesiophobia (TSK-11SV) [68,69] is a questionnaire that allows us to measure the fear of moving or being injured/(re)injured in patients with pain. There is a reduced version that is validated in Spanish and is called TSK-11SV. This scale consists of a questionnaire, which contains 11 items in its reduced version. Scores range from one to four points with a response of “strongly disagree”, meaning one point; “partially disagree”, two points; “partially agree”, three points; and “strongly agree”, 4 points. To obtain a total final score, the sum of the items is required. The final score can be at least 11 and at most 44 points. The higher the score, the higher the degree of kinesiophobia.

The Chronic Pain Acceptance Questionnaire (CPAQ) [70,71] consists of 20 items that assess 2 main factors: “willingness or involvement in activities” (activity engagement) and “acceptance or openness to pain” (pain willingness). Respondents rate each of the 20 items on a scale from 0 (never true) to 6 (always true). Nine of these items measure acceptance or openness to pain (items 4, 7, 11, 13, 14, 16, 17, 18, and 20), and eleven measure willingness or involvement in activities (items 1, 2, 3, 5, 6, 8, 9, 10, 12, 15, and 19). The total score of the questionnaire is the sum of the direct items of involvement in activity engagement, plus the sum of the items measuring pain willingness. The maximum possible total score is 120, with higher scores indicating greater pain acceptance.

The Psychological Inflexibility of Pain Scale (PIPS) [72,73,74] consists of 12 items that assess 2 main factors, known as avoidance and cognitive fusion, on a 7-point Likert-type scale ranging from “never” to “always true”. Higher PIPS scores indicate lower psychological flexibility.

The SF-12 Health Questionnaire (SF-12) [75] is composed of a subset of 12 items from the SF-36, from which the physical and mental summary components of the SF-12 are constructed as single scores. There are 12 items, with 8 dimensions and 2 summative components (physical and mental). The response options form Likert-type scales that assess the intensity or frequency. The number of response options ranges from three to six, depending on the item. Values higher or lower than 50 should be interpreted as better or worse, respectively, than the reference population. For each of the 8 dimensions, the items are coded, aggregated, and transformed into a scale that ranges from 0 (the worst state of health for that dimension) to 100 (the best state of health).

The Oswestry Low Back Pain Disability Scale (OLBPDQ) [76,77] is a questionnaire specific for LBP that measures limitations in daily activities. It consists of 10 questions with 6 possible answers each. The first question refers to the intensity of the pain, specifying in the different options the response to taking analgesics. The remaining items include basic activities of daily living that can be affected by pain (i.e., self-care, lifting weights, walking, sitting, standing, sleeping, sexual activity, social life, and travel). The scale has 10 questions with 6 possible answers each. Each item is valued from 0 to 5, from least to most limiting. If the first option is marked, 0 is scored and 5 if the last option is indicated. The total score, expressed as a percentage (from 0 to 100%), is obtained by summing the scores for each item, divided by the maximum possible score multiplied by 100. Higher values describe greater functional limitation. Score ranges are as follows: 0–20%, minimal functional limitation; 20–40%, moderate; 40–60%, intense; 60–80%, disability; and above 80%, maximum functional limitation.

### 2.6. Statistical Analysis

Data analyses will be carried out using the statistical packages SPSS v26.0, R with R Studio v4.0.2, and MPlus v7.4. Comparative analyses of continuous data will be performed using the Student’s *t* test or their non-parametric equivalents (i.e., Mann–Whitney U or Kruskal–Wallis test), depending on the characteristics inherent to the variables under study. The Chi-Square test or Fisher’s exact test will be used, as appropriate, for categorical variables. The Bonferroni correction will be applied in all post hoc tests. In all statistical tests performed with the outcome variables, a statistical significance level of 0.05 will be used. In adherence with CONSORT recommendations, potential baseline differences in sociodemographic and clinical characteristics are considered irrelevant after randomization and, as a result, were not included as covariates in the analyses of RCT outcomes.

The main analysis will compare the effect ACT compared to TAU on the primary outcome (pain intensity and pain interference at 12-month follow-ups). All data analyses will be carried out following an intention-to-treat (ITT) principle, that is, regardless of protocol adherence. Then, we will compute analysis of the primary outcome post-treatment and analysis of the secondary and treatment process outcomes at post-treatment and at 12-month follow-up. The analyses will be replicated from a per-protocol approach. Multi-level, linear mixed models will be created using the restricted maximum likelihood method for the estimation of parameters. The effect sizes will be calculated according to Cohen’s *d*. A 5% significance level will be used in all 2-tailed tests, applying the Benjamini–Hochberg correction for multiple comparisons (to reduce the risk of false positives).

To determine the clinical significance of improvements on the primary outcome (BPI), patients will be classified into two categories: responders and non-responders. Considering the Initiative on Methods, Measurement, and Pain Assessment in Clinical Trials (IMMPACT) recommendations, a 1-point reduction in the pre–post and pre-follow-up BPI total score are used as a criterion for establishing clinically significant improvement [78]. This categorization was also used to calculate the number needed to treat (NNT) in TAU + ACT compared to TAU, with a 95% confidence interval (CI) calculated for each NNT at post-treatment and at follow-up. Furthermore, between-group differences in sociodemographic and clinical characteristics, and outcomes at baseline, post-treatment, and follow-up will be examined for responders versus non-responders using the Chi-Square test or Fisher’s exact test and Student’s *t*-tests for categorical and continuous variables, respectively.

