## Abstract

Research on the use of Acceptance and Commitment Therapy (ACT) for patients with degenerative lumbar pathology awaiting surgery are limited. However, there is evidence to suggest that this psychological therapy may be effective in improving pain interference, anxiety, depression, and quality of life. This is the protocol for a randomized controlled trial (RCT) to evaluate the effectiveness of ACT compared to treatment as usual (TAU) for people with degenerative lumbar pathology who are candidates for surgery in the short term. A total of 102 patients with degenerative lumbar spine pathology will be randomly assigned to TAU (control group) or ACT + TAU (intervention group). Participants will be assessed after treatment and at 3-, 6-, and 12-month follow-ups. The primary outcome will be the mean change from baseline on the Brief Pain Inventory (pain interference). Secondary outcomes will include changes in pain intensity, anxiety, depression, pain catastrophizing, fear of movement, quality of life, disability due to low back pain (LBP), pain acceptance, and psychological inflexibility. Linear mixed models will be used to analyze the data. Additionally, effect sizes and number needed to treat (NNT) will be calculated. We posit that ACT may be used to help patients cope with the stress and uncertainty associated with their condition and the surgery itself.

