It is hoped that ACT will improve the results in variables studied in relation to chronic pain in this population at high risk of postsurgical LBP. This study is justified because of the importance of identifying these psychosocial prognostic factors, and to be able to intervene with them, to improve the clinical outcomes of surgical treatment in patients with chronic degenerative LBP. The purpose is to apply ACT to improve these outcomes. Of the patients who are candidates for lumbar surgery, those with a high fear of movement (kinesiophobia), a high level of catastrophism, and the presence of anxiety and depression will be screened to focus the intervention on them. The ACT program has been designed to develop skills and tools with patients to enable them to regulate themselves in the face of pain, fear of movement, catastrophizing, anxiety, and depression. By applying this intervention, we will seek to improve pain acceptance and psychological flexibility with the idea of improving catastrophizing, kinesiophobia, anxiety, depression, quality of life, and overall personal functioning of people with chronic pain both before and after surgery, as measured by the degree of pain interference (primary endpoint of our study).

Predicting the prognosis in patients scheduled for surgery for LBP, through previous evaluation tests, could be efficient to apply them to complementary treatment modalities and thus prevent the chronification of pain and the worsening of functionality. People with chronic degenerative LBP who are candidates for surgery, with higher rates of catastrophizing, anxiety, depression, and fear of movement (kinesiophobia) will present a higher risk of chronic pain and a worse prognosis in relation to the efficacy of surgical treatment. We posit that participants receiving ACT will have greater improvement in pain intensity, pain interference, and quality of life, and less disability than participants receiving only TAU. It is hoped that ACT can improve the results in the variables studied in relation to chronic pain in this population with a high postsurgical risk of LBP.

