Sociodemographic and clinical questionnaire	X				
Primary outcome measure					
BPI (pain interference)	X	X	X	X	X
Secondary outcome measures					
BPI (pain intensity)	X	X	X	X	X
HADS (anxiety and depression)	X	X	X	X	X
PCS (pain catastrophizing)	X	X	X	X	X
PIPS (psychological inflexibility to pain)	X	X	X	X	X
TSK-11SV (fear of movement)	X	X	X	X	X
CPAQ-20 (pain acceptance)	X	X	X	X	X
SF-12 (health-related quality life)	X	X	X	X	X
OLBPDQ (functional status)	X	X	X	X	X

Note: BPI = Brief Pain Inventory-Interference Scale; HADS = Hospital Anxiety and Depression Scale; PCS = Pain Catastrophizing Scale; PIPS = Psychological Inflexibility in Pain Scale; TSK-11SV = Tampa Kinesiophobia Scale; CPAQ-20 = Chronic Pain Acceptance Questionnaire; SF-12 = Short-Form 12 Health Survey; OLBPDQ = Oswestry Low Back Pain Disability Scale.

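### The reason given for leaving baseline characteristics out of the outcome models does not justify forgoing adjustment for baseline pain interference, and the plan states no baseline-adjusted analysis

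*Protocol article*

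**What the plan says.** Section 2.6 sets one rule on covariates, citing CONSORT. Of sociodemographic and clinical variables on which the arms might differ at baseline, it says that they "are considered irrelevant after randomization and, as a result, were not included as covariates in the analyses of RCT outcomes".

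The Abstract defines the endpoint as a change: "The primary outcome will be the mean change from baseline on the Brief Pain Inventory (pain interference" scale). Section 2.6 describes the model only as far as its type and estimation method: "Multi-level, linear mixed models will be created using the restricted maximum likelihood method for the estimation of parameters". It places the main analysis at 12 months. Neither place says how the baseline measurement enters the model.

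Table 2 schedules BPI interference at the pre-treatment visit and at four later visits, so the baseline score will be collected. The same table schedules a pre-treatment measurement of every secondary outcome.

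**The concern.** Two ideas are run together. Randomization makes a significance test of baseline differences uninformative, because any difference is due to chance. Adjustment for a baseline value that predicts the outcome has a different purpose: it removes explained variation from the treatment comparison, whether or not an imbalance is seen. The stated reason answers the first matter and is used to settle the second.

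An unadjusted change score uses the baseline, but with a fixed weight of one. Unless r is 1, that weight is too large. The result is extra variance, and a chance baseline difference is carried into the estimate in the opposite direction. In a trial that expects to keep about 36 patients per arm, this precision is worth having.

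**Working it through.** **Inputs from the protocol (sections 2.2 and 2.6).** 51 per arm; 30% dropout; two-sided 5%; 80% power; Cohen's d of 0.64 at post-treatment and 0.73 at follow-up.

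**Input not in the protocol.** The correlation r between baseline and follow-up BPI interference. It is assumed here, over the range 0.3 to 0.7.

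**The plan's own figure.** By the normal approximation, n = 2(1.960 + 0.842)²/0.64² = 38.3, so 39 per arm. Then 39 × 1.3 = 50.7, so 51, as stated. After 30% loss, 51 × 0.7 = 35.7 per arm remain evaluable. A plain comparison of follow-up scores then has 76% power at d = 0.64 and 86% at d = 0.73.

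**Variances.** Take equal SDs at baseline and follow-up, and express each variance relative to a comparison of follow-up scores alone:

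- follow-up only: 1
- change score, or a group-by-time contrast with baseline means free in each arm: 2(1 − r)
- baseline as covariate, or a mixed model with baseline means held equal: 1 − r²

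A generalised least squares calculation gave the same mixed-model values: 1.40 against 0.91 at r = 0.3, 1.00 against 0.75 at r = 0.5, and 0.60 against 0.51 at r = 0.7.

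The ratio of adjusted to change score is (1 − r²)/[2(1 − r)] = (1 + r)/2. Since 2(1 − r) − (1 − r²) = (1 − r)², the change score is never the more precise of the two.

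**Power.** Noncentral t, 35.7 per arm, d on the follow-up SD. The effective d is d/√[2(1 − r)] for the change score and d/√(1 − r²) with adjustment. Cells show change score vs adjusted.

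| Assumed r | Variance ratio (1+r)/2 | d = 0.64 (post-treatment) | d = 0.73 (follow-up) |
|---|---|---|---|
| 0.3 | 0.65 | 62% vs 80% | 73% vs 89% |
| 0.5 | 0.75 | 76% vs 87% | 86% vs 94% |
| 0.6 | 0.80 | 85% vs 92% | 93% vs 97% |
| 0.7 | 0.85 | 93% vs 96% | 98% vs 99% |

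The d = 0.73 column is the one that applies to the main 12-month analysis. The gain over a change score shrinks as r rises: 16, 8, 4 and 1 points.

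**If d is on the change-score SD instead.** Change-score power is then 76% at d = 0.64 whatever r is. Adjusted power, with effective d of 0.64/√[(1 + r)/2], is 91%, 87%, 85% and 82% for the four values of r. The direction is the same.

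**Chance imbalance.** If the arms differ by δ at baseline, the change-score estimate is expected to shift by (1 − r)δ in size: 70%, 50%, 40% and 30% of δ for the four values of r. Adjustment removes this shift.

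**The case against.** A reader might infer that the plan bars every baseline covariate and throws the baseline BPI score away. The text does not support that.

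- The rule names sociodemographic and clinical characteristics. Elsewhere in section 2.6 baseline outcomes are listed as a separate item: "between-group differences in sociodemographic and clinical characteristics, and outcomes at baseline, post-treatment, and follow-up will be examined". Table 2 also places BPI outside its block of sociodemographic, clinical and screening measures. Whether clinical characteristics cover BPI is therefore ambiguous.
- A change score already uses part of the baseline information. So does a mixed model with the pre-treatment visit as a response. If that model held the baseline means equal, it would reach the adjusted precision with no covariate.
- Fixed effects are commonly left to a statistical analysis plan, which is not shown here.

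These points stand, and they narrow the finding. They do not remove it. The finding is not that the plan is silent on model terms. The plan states a rule on covariates whose reason does not support it, the rule can be read to exclude baseline BPI, and the only stated form of the primary outcome is the less efficient one.

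Two further inferences would also go too far. The first is that the main analysis falls short of its 80% target. At d = 0.73 that happens only for the change score at the lowest r shown. The second is that the protocol itself calls baseline BPI interference prognostic. The Discussion says that people with higher catastrophizing, anxiety, depression and kinesiophobia "will present a higher risk of chronic pain and a worse prognosis in relation to the efficacy of surgical treatment". That sits badly with calling baseline characteristics irrelevant, but it concerns psychological scores and not BPI interference.

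**Conclusion.** The concern holds as a matter of efficiency and of a misapplied rationale. The unadjusted analysis is unbiased across repeated trials, so validity is not at stake. What is lost is precision, together with protection against the baseline imbalance that happens to occur in this one trial.

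Against a change score or an unconstrained group-by-time contrast, adjustment cuts the variance by 35%, 25%, 20% and 15% at r = 0.3, 0.5, 0.6 and 0.7. At the follow-up effect size this is a gain of between 16 points of power and 1 point. Surgery falls between baseline and the 12-month visit, so a lower r, where the gain is largest, is plausible; the protocol gives no figure to settle it.

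The sizes assume equal SDs over time, the same r in both arms, d on the follow-up SD, and patients with complete data only. They ignore the one degree of freedom spent on the covariate.

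**What to change.** Replace the covariate sentence in section 2.6 with wording such as:

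> No significance tests of baseline differences will be done. Each mixed model includes the baseline value of its outcome as a fixed covariate (with its interaction with visit), or constrains the baseline means to be equal in both arms.

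One of the two forms should be chosen and applied to the primary and all secondary outcomes. The choice must be fixed before data are analysed, because adjustment chosen afterwards would be open to challenge.

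The cost is a change of wording and one model term. Table 2 already schedules every baseline score needed, so no extra visits, patients or measurements are required.
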